## **6.2 Criteria for Patient Discontinuation**

Patients will not be able to discontinue treatment prior to end of intervention in the present trial but can discontinue after end of intervention but before the 28-day follow-up.

If SpO2 is < 50% at any point after allocation/randomization the patient case can be emergency unblinded and treatment continued as decided by study doctor. In case of cardiac arrest, INO is continued at the discretion of the study doctor. In case a serious adverse reaction triggered by IMP is suspected, an emergency blinding should be performed, and treatment with IMP discontinued or continued at the discretion of the study doctor.

## **6.3 Trial Discontinuation**

The whole trial may be discontinued at the discretion of the PI or the sponsor in the event of any of the following:

- Occurrence of AEs unknown to date in respect of their nature, severity and duration
- Medical or ethical reasons affecting the continued performance of the trial
- Difficulties in the recruitment of patients
- At sponsors discretion

The sponsor and principal investigator will inform all investigators, the relevant Competent Authorities and Ethics Committees of the termination of the trial along with the reasons for such action. If the study is terminated early on grounds of safety, the Competent Authorities and Ethics Committees will be informed within 15 days.

## **6.4 Laboratory Tests**

There will be no specific laboratory test performed on participants in this trial beyond standard clinical practice. There will be no biobank established.

All laboratory test in this trial will be performed in accordance with Oslo University Hospital and laboratory standard procedures.

# **7 ASSESSMENTS**

## **7.1 Assessment of Efficacy**

### **7.1.1 Primary endpoint: Oxygen saturation**

Hypoxemia is one of the key features of COVID-19 related respiratory failure. Hypoxia may lead to serious brain damage, cardiac arrest and death. In susceptible patients, hypoxia may trigger acute serious diseases such as myocardial infarction and stroke. Mechanical ventilation is the mainstay in the treatment of hypoxia in COVID-19. To establish mechanical ventilation the patient needs an endotracheal tube (ETT). This is established through a rapid sequence intubation (RSI) procedure. During this procedure, the risk of severe

hypoxia is aggravated. Maintaining a higher oxygen saturation is therefore considered beneficial. Measuring SpO2 is a direct reflection of what we aim to achieve with this treatment and is therefore chosen as the primary endpoint (1.1.1 table).

Oxygen saturation is the percentage of haemoglobin binding sites occupied by oxygen in the blood ( $\text{HbO}_2/(\text{HbO}_2+\text{Hb})$ ). The peripheral oxygen saturation (SpO2) is an approximated measure of arterial oxygen saturation and is measured non-invasively by pulse oximetry. The pulse oximeter uses a light emitting diode in conjunction with a light-sensitive sensor that measures the absorption of red and infrared light in the extremity. The SpO2 is calculated from the difference between oxygenated and deoxygenated haemoglobin. Oxygen saturation is a routinely used measurement of patient oxygenation. Sources of error such as nail polish, ambient infra-red or ultraviolet light will be considered as per normal routine.

There is no cut-off value where we can decide whether hypoxia is harmful for the patient or not. This will be dependent on other clinical features of the patient. For the primary endpoint we therefore choose to evaluate the change in SpO2 as a continuous variable. According to general anaesthetic practice, increasing the SpO2 to as close to 100% as possible is considered desirable prior to RSI. Thus, any increment in SpO2 is considered beneficial. For this study we assume that an increase in SpO2 of 5 percentage points prior to RSI is a reasonable estimate of what is clinically significant.

### 7.1.2 Secondary endpoints:

#### Primary objective

The time to effect of iNO in these patients is uncertain. For the same reasons as for the primary endpoint we have included increase in SpO2 after 10 minutes as a secondary endpoint (1.2.1)

The overall cellular stress during hypoxemia is affected both by the degree of hypoxia and the length of the hypoxic insult. The longitudinal changes in SpO2 during the intervention (1.2.2) is therefore a valid marker of the efficacy of the INO treatment.

Oxygen saturation during RSI (1.2.3) is a value subject to several factors that cannot be controlled for in this study. This is presumably however an important value in predicting cerebral or cardiac stress and disease. When SpO2 falls below 50% the accuracy of measurement is low. At the same time, this value has certainly potential for causing serious brain or cardiac damage. The number of patients with this low SpO2 therefore included as a secondary endpoint (1.2.4). Respiratory rate (1.2.5) reflects hypoxic drive and is expected to fall as SpO2 increases. Arterial blood gas analyses (1.2.6 and 1.2.7) are not easily obtainable in the prehospital environment but is considered a more accurate reflection of oxygen saturation. Where available, this measurement will be included in the analyses. On the extreme, cardiac arrest or severe bradycardia (1.2.8) are markers of hypoxemia with potentially lethal consequences and are included in the secondary analyses. Glasgow Outcome Score Extended (GOS-E) may reflect brain damage as a result of hypoxia (1.2.9). Mortality in 24 hours (1.2.9) are may be direct result of hypoxemia in this patient group and may as such be an important marker for the efficacy of iNO. Mortality at 28 days is relevant as late complications following hypoxemia may manifest at this stage.

#### Secondary objectives

The endpoints of the secondary objectives reflect the known adverse effects of INO. Although this are not described after short-term administration, they will be included in this study. Both bradycardia and hypotension are possible side effects of NO. Both heart rate and blood pressure will be monitored during the intervention phase, and samples every 5 minutes are used as endpoints. (2.1.1 and 2.1.2)

All other secondary outcome parameters are collected from the patient journal.

Acute kidney injury is classified in three stages according to KDIGO. (2.2.2) A more sensitive but less specific marker of kidney function is the change in serum urea concentration. (2.2.1). Both measures are gathered on the 28-day follow-up, and the value most strongly indicative of kidney failure is used for this endpoint. Platelet count, Methaemoglobinaemia is collected from the patients EPJ.

Data from patient monitor measuring impedance (ohms) will be used to calculate respiratory rate.

## **7.2 Safety Considerations and Assessments**

Safety will be monitored by the assessments described below as well as the collection of AEs. For details on AE collection and reporting see chapter 8. and assessment schedule refer to Flow chart in Section 6.

### **Rebound reactions**

Following abrupt discontinuation of iNO treatment this is well recognized. Rebound reaction is manifested as increased pulmonary arterial pressure, with a subsequent drop in SpO2. The effect is mediated through downregulation of endogenous NO production. Experimentally these changes are limited during the first couple of hours of iNO treatment(14). Moreover, at least one clinical study indicate that rebound does not occur after short term treatment of 30 minutes(15). For safety reasons, iNO in this study will be gradually weaned under careful observation. (See Ch 5.3)

### **Renal toxicity**

Renal impairment is a well described complication to INO, although it is not described in the SPC. All previous studies in adults are in intensive care unit patients, who are exposed to INO, often over several days, and much longer than patients are exposed to IMP in the current trial. We will evaluate renal function in all included patients using the Kidney Disease: Improving Global Outcomes (KDIGO)(16)

### **Monitoring formation of nitrogen dioxide (NO2)**

NO2 rapidly forms in gas mixtures containing nitric oxide and O2, and nitric oxide may in this way cause airway inflammation and damage. When administering iNO in the ICU, monitoring of concentration of nitrogen dioxide is mandatory. As a result, NO2 sensors are built into INO delivery systems such as INOmax DSIR® Plus Delivery Systems. These systems are made for long-term delivery of iNO in closed circuits.

The present study uses the INOblender, with no measurement of NO2. This is accounted for in the product specification where the issue of NO2 build up is counteracted with constant flow through the system. If the gas mix is not moving through the circuit due to absent ventilation a purge procedure is described. The manual bag should be squeezed repeatedly during use to avoid NO2 building up in the bag.

In the present trial this will not be a big issue, as there will be constant flow through the system as iNO is started. The patient will be breathing spontaneously in a bag/mask system already.

After intubation or other for any reason the bag has been idle the bag should then be purged prior to recommencing ventilation.

There will be no measurement of NO2 formation in this trial.

### **Monitoring formation of methaemoglobin**

According to INOmax Highlights Of Prescribing Information (attached), the mean methaemoglobin level remained below 1% in the placebo group and in the 5 ppm and 20 ppm INOmax groups, in neonates. We expect methaemoglobin formation unlikely in our dosing range and time of administration.

Methaemoglobin will be measured upon arrival to hospital as part of the arterial blood gas analysis which will be routinely sampled in these patients. We will generally conform to the advice set out in the SPC, and measure methaemoglobin within one hour of the initiation of INOmax therapy.

The highest level of methaemoglobin measured during the treatment period of this trial will be recorded in the CRF.

### **Effects on platelets**

According to the SPC, regular monitoring of haemostasis and measurement of bleeding time is recommended during the administration of INOmax for more than 24 hours. This falls outside of the time patients in this trial will receive INO. We do not intend to specifically analyze and assess platelet function and haemostasis in our trial.

### **Occupational exposure**

The INOblender product specification recommendation for occupational exposure to NO and NO2 is based on average exposure over an 8-hour time period. This exceeds the study period in the present trial. The delivery of INO in the present trial represents a low dosing (20 ppm). The delivery circuit will be closed for the majority of the time during which personnel is in contact with the system. To protect staff any pregnant staff present is an exclusion criterion in this trial.

The use in the current protocol does not deviate from current practice in Oslo University Hospital, where iNO and the INOblender is in regular use for patient care in both helicopters, ambulances and the hospital. There will be no measurement of N2 or NO in the work environment during this trial.

For reference the Norwegian exposure limits are as follows: NO2 8 hours exposure - 0,5 ppm, or 0,96 mg/m^3; NO2 15 minutes exposure - 1ppm, or 1,91 mg/m^3; and NO xx min exposure 2 ppm, or 2,5 mg/m^3(17).

## **7.3 Risk/ benefit balance of the trial**

To balance these two concepts, we have 1) identified the risks and minimized them and 2) described potential benefits to individual subjects, groups of patients and society and attempted to enhance them.

### **Risks Identified and mitigating efforts**

1. Research on critically ill patients: Participants included in this trial are critically ill, and require expedient and skillful medical interventions. They suffer time- critical pathology and will often be recruited outside of hospital in an environment that may be challenging to emergency medical staff.

All investigators in this s trial work with these patients and in the pre-hospital or emergency department environment on the daily basis. They are specifically trained, and all their equipment and operating procedures designed for the exact patient group recruited in this trial.

2. Delay in standard care: As described in the introduction treatment following the Airway, Breathing and Circulation principles are the core in the treatment of the patients recruited in this trial. Rapid Sequence Intubation is a key part of the management in these patients, indeed the safest possible RSI is the objective of this trial. In our design the time from arrival to the patient until allocation is 3 minutes, with additional 5 minutes of bag/ mask + PEEP after allocation to treatment arm. These 8 minutes does not constitute any considerable delay in treatment for participants included in the trail compared to patients treated outside of protocol. The 8 minutes will be filled by preparation for RSI

beyond the preoxygenation (with or without INOmax). Paramedic staff and others will use this time to do all the other preparations necessary for a safe and successful RSI:

- a. The preparation of medication for sedation, analgesia and muscle relaxation- including efforts to prevent medication errors and needle-stick injury
  - b. The establishing and securing of intravenous or intraosseous access for medication administration
  - c. The preparation of equipment for RSI: laryngoscope, device to secure endotracheal tube, suction device with extra filter for Sars COV-2 protection
  - d. The preparation of the patient and environment, including lifting to gurney while bag/mask ventilating, clearing out furniture or other objects blocking, evacuating patient to more suitable location, e.g. outside or inside ambulance.
3. Adverse Events to the Administration of IMP: The Marketing Authorization of the IMP does not include acute respiratory failure caused by viral infections as a therapeutic indication. Temporary administration of the IMP is however widely used in acute respiratory failure of similar etiology. No modifications will be made to the equipment. INO is generally well tolerated. Data on adverse Events in the literature generally report INOmax exposure over days or hours, while this trial propose a very short exposure. There is an extensive AE/SAE reporting procedure in place and a DMC who monitors the trial. The most acute adverse event anticipated is a rebound reaction. All investigators are trained anaesthetists, with study specific training to recognize and handle such reaction.
4. INOmax may not work, or it may not be better than the standard treatment. In this case we believe standard care is acceptable, and that adding INOmax does not reduce the quality of standard care.

### **Benefit and efforts to maximize this**

1. Individual participants: There is a potential benefit in receiving new treatment as part of RSI before it is available to everyone.
2. Individual participants: Knowing that the knowledge gained may benefit others in the future.
3. Transparency/ Sharing of data: The data sharing policy is important in all clinical research, particularly when a data regarding an emerging pandemic is studied, so that others may use this to increase our knowledge. This is important to maximize benefit.

The risk/ benefit balance is the representation of the principles of non-maleficence (first: do not harm) and beneficence (act to the benefit of others). It cannot be calculated from a mathematical formula, but we believe this study is designed in favour of beneficence.

## **8 SAFETY MONITORING AND REPORTING**

The investigator is responsible for the detection and documentation of events meeting the criteria and definition of an adverse event (AE) or serious adverse event (SAE).

Please note that in the present trial all included participants are expected to meet one or more criteria for serious adverse events. The nature of the patient population studied, the prehospital environment, severity of illness included, and multitude of medical interventions makes the AE reporting challenging. Several events that meet the AE criteria set out in GCP are expected in the natural history of critical illness and in the treatment offered to patients included in this trial. On this basis we find support in the literature to prespecify outcomes that would be reported as AEs in other trials but are expected outcomes in the present. This system has previously been used in randomized trials of INO in congenital heart disease(18, 19).

### **8.1 Definitions**

#### **8.1.1 Adverse Event (AE)**

An AE is any untoward medical occurrence in a patient administered a pharmaceutical product and which does not necessarily have a causal relationship with this treatment.

The term AE is used to include both serious and non-serious AEs.

#### **8.1.2 Serious Adverse Event (SAE)**

Any untoward medical occurrence that at any dose:

- Results in death
- Is immediately life-threatening
- Requires in-patient hospitalization or prolongation of existing hospitalization
- Results in persistent or significant disability or incapacity
- Is a congenital abnormality or birth defect
- Is an important medical event that may jeopardize the subject or may require medical intervention to prevent one of the outcomes listed above.

Medical and scientific judgment is to be exercised in deciding on the seriousness of a case. Important medical events may not be immediately life-threatening or result in death or hospitalization but may jeopardize the subject or may require intervention to prevent one of the listed outcomes in the definitions above. In such situations, or in doubtful cases, the case should be considered as serious. Hospitalization for administrative reason (for observation or social reasons) is allowed at the investigator's discretion and will not qualify as serious unless there is an associated adverse event warranting hospitalization.

#### **8.1.3 Adverse Reaction (AR):**

Events deemed to have a Certain, Probable/ Likely or Possible causal relationship of the event to IMP will be classified as an Adverse Reaction.

#### **8.1.4 Suspected Unexpected Serious Adverse Reaction (SUSAR)**

Suspected Unexpected Serious Adverse Reaction: SAR that is unexpected possibly related to INO.

## 8.2 Expected Adverse Events

### 8.2.1 Expected Adverse Events from Inhaled NO

Please consult the Summary of product characteristics for INOmax 800 ppm mol/mol medicinal gas for complete safety information.

In summary the most frequent expected AE is the rebound reaction, defined as “Abrupt discontinuation of the administration of inhaled nitric oxide may cause rebound reaction; decrease in oxygenation and increase in central pressure and subsequent decrease in systemic blood pressure. Rebound reaction is the most commonly adverse reaction in association with the clinical use of INOmax. The rebound may be seen early as well as late during therapy.”

The duration of therapy of INOmax in this SPC is up to 7 days in the peri-operative setting, and common treatment times are 24 -48 hours. In the present trial the treatment time is expected to be substantially shorter, we expect this to reduce the risk of all adverse events.

| Summary Of Product Characteristics 4.8 Undesirable effects |                  |             |                   |      |           |                                                           |
|------------------------------------------------------------|------------------|-------------|-------------------|------|-----------|-----------------------------------------------------------|
| System organ class                                         | Very common      | Common      | Uncommon          | Rare | Very rare | Not known                                                 |
| Blood and lymphatic system disorders                       | Thrombocytopenia | -           | Methemoglobinemia | -    | -         | -                                                         |
| Cardiac disorders                                          | -                | -           | -                 | -    | -         | Bradycardia (following abrupt discontinuation of therapy) |
| Vascular disorders                                         | -                | Hypotension | -                 | -    | -         | -                                                         |
| Respiratory, thoracic and mediastinal disorders            | -                | Atelectasis | -                 | -    | -         | Hypoxia
Dyspnoea
Chest Discomfort
Dry throat     |
| Nervous system disorders                                   | -                | -           | -                 | -    | -         | Headache
Dizziness                                     |

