### 6.1.2 Treatment

The doctor's assistant, who is specifically trained for the procedure, will open a sealed envelope with information on patient allocation, and either open or leave the INO cylinder closed accordingly. If randomized to only O2 a simulated cylinder opening will be undertaken. Regardless of randomization the INOBlender is set to deliver 20 ppm. SpO2 is recorded at time of allocation ( $t_0$ ) and after 5 minutes ( $t_1$ ). Other vital signs are automatically and continuously recorded in the internal memory of the patient monitor and extracted at 5 minute intervals to EOI ( $t_0$  to  $t_n$ ).

If the patient is included outside hospital, the doctor makes the decision to either perform RSI prior to transportation or continue current treatment during transport to hospital.

At the time the clinician decides to perform RSI, the lowest SpO2 during the RSI-procedure is recorded ( $t_{RSI}$ ) regardless of where the procedure is performed.

In any event where the bag/mask/valve is left idle, four normal tidal volumes must be ventilated into free air before re-connected to patient in order to purge the system of any NO2 build up.

Blood samples, physiological data and clinical scoring made after EOI is done as indicated by local routines regardless of the study. Relevant clinical data is retrieved from the institution's patient journal on follow-up at day 28 post admission.

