### 6.1.3 End of Intervention

End of intervention is defined as the time point where INO administered by the INOBlender is discontinued.

This may be on different time points before transport, during transport or in hospital. For patients still requiring INO, the receiving hospital INO must be delivered by another INO device, and is no longer defined as IMP.

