| Vascular disorders                              | 
 
• Acute hypotension
 
                                                                                                                                                                                                  |

Please note: Both suspected rebound reactions and death prior to end of intervention will always be reported to Sponsor as a serious adverse event.

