### 8.3 Time Period for Reporting AE and SAE

- For each patient the standard time period for collecting and recording AE will be from allocation and until End of Intervention
- For each patient the standard time period for collecting and recording SAE will be from allocation and until the 28 day follow up visit. At the 28 days visit an assessment will be made where we specifically ask for all SAEs mentioned in chapter 8.2. We will also assess discharge notes and treating physician for other events that fulfil the SAE definition and that can be assessed by the study team.
- For patients still admitted to hospitals at day 28 an effort will be made to secure access to main discharge note for assessment for any SAE that has occurred between day 28 and discharge.
- Any information that comes to investigators attention for any included patient prior to End of Trial will be assessed according to this protocol

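### Planned 5-minute vital-sign readings and non-serious AE recording stop when blender INO stops, so no timed reading follows the final 5-to-0 ppm step or an unplanned stop

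*Protocol*

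**What the plan says.** - **The hazard.** Section 8.2.1: "In summary the most frequent expected AE is the rebound reaction". The trigger it gives is abrupt withdrawal of INO. Section 7.3 also singles out rebound as the most acute event foreseen.
- **End of intervention.** Section 6.1.3: "End of intervention is defined as the time point where INO administered by the INOBlender is discontinued".
- **Timed readings.** Section 6.1.2 says vital signs are "automatically and continuously recorded in the internal memory of the patient monitor and extracted at 5 minute intervals to EOI" and equates that span with t0 to tn. The SpO2 series (endpoint 1.2.3, t1 to tn) therefore ends at the same point. On the circulatory safety endpoints, section 7.1.2 says: "Both heart rate and blood pressure will be monitored during the intervention phase, and samples every 5 minutes are used as endpoints".
- **Adverse events.** Section 8.3: "For each patient the standard time period for collecting and recording AE will be from allocation and until End of Intervention". SAEs run to the day-28 visit, where "an assessment will be made where we specifically ask for all SAEs mentioned in chapter 8.2".
- **Rebound reporting.** Section 8.2.2: "Both suspected rebound reactions and death prior to end of intervention will always be reported to Sponsor as a serious adverse event".
- **Weaning.** Section 5.3 lowers the dose by 5 ppm every 5 minutes from 20 ppm.
- **Common anchor.** Section 6.1.2: "Regardless of randomization the INOBlender is set to deliver 20 ppm".

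**The concern.** The protocol's leading expected hazard is a response to withdrawal, yet the planned objective measurements close at the instant of withdrawal. A fall in SpO2 or blood pressure in the minutes afterwards that is not serious, and that nobody calls rebound, leaves no planned timed value to compare between arms. Endpoints 1.2.4 (SpO2 below 50) and 1.2.7 (cardiac arrest) close with the intervention as well.

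The remaining early signal is the count of suspected rebound. In hospital, some of those judging it may know the allocation, because section 10.2 hands the envelope to the receiving staff at the same point at which section 5.3 starts the in-hospital wean. A count formed that way could err in either direction: too low if falls go unrecognised, too high in the INO arm if knowing the allocation makes the label come more readily. An objective reading in both arms would help a reader interpret it.

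**Working it through.** The plan states no figure for this point, so the check is a count of readings against weaning steps.

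**Inputs.** Start dose 20 ppm, steps of 5 ppm every 5 minutes (5.3); readings every 5 minutes until EOI (6.1.2); EOI is the stop of blender INO (6.1.3).

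**Number of reductions.** 20 / 5 = 4. With the first reduction at minute 0, they fall at minutes 0, 5, 10 and 15. The last, at minute 15, is the stop and therefore EOI.

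**Planned readings after each reduction, up to EOI:**

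| Reduction | Minute | Readings after it | Count |
|---|---|---|---|
| 20 to 15 ppm | 0 | 5, 10, 15 | 3 |
| 15 to 10 ppm | 5 | 10, 15 | 2 |
| 10 to 5 ppm | 10 | 15 | 1 |
| 5 to 0 ppm | 15 | none | 0 |

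The reading at minute 15 is taken at the stop, not after it. The counts do not depend on the clocks being aligned. With readings at minutes 2, 7 and 12, for example, they are again 3, 2, 1 and 0.

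**Unplanned stop.** Section 6.2 lets the study doctor discontinue INO after a suspected serious reaction. Under 6.1.3 that is also EOI, so no planned reading follows it. Such a stop may be abrupt, which is the trigger named in 8.2.1.

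**Allocation in hospital.** The wean (5.3) and the envelope handover (10.2) share one trigger: arrival, then intubation or a decision against it. If the first reduction is made at the trigger, 0 ppm is reached 3 x 5 = 15 minutes later. If it is made 5 minutes after the trigger, 0 ppm is reached at 20 minutes. Receiving staff can therefore know the allocation before the last step.

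**What is still collected after EOI:**

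- Suspected rebound, as an SAE to day 28 (8.2.2, 8.3).
- Serious acute hypotension, bradycardia, cardiac arrest and brain hypoxia. All are listed in 8.2.2 and asked about at day 28 without needing a rebound label.
- Need for INO after EOI, with start time, duration and dose (2.5.1).
- The lowest PaO2/FiO2 in the first 24 hours in ventilated patients (3.1.1), which is not tied to the stop.

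The remainder is non-serious or unrecognised change just after the stop.

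**Effect of extending by 15 minutes.** 15 / 5 = 3 readings after the stop, instead of 0.

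**The case against.** **Rebound is tied to abrupt withdrawal, and the plan avoids that.** Section 7.2 says the changes are limited in the first hours of treatment, cites a clinical study indicating none after 30 minutes, and weans gradually under observation. This stands: a weaned 5-to-0 ppm step is a lower-risk trigger. It does not close the point. The intervention is estimated at one hour with wide variation (section 3), unplanned stops are allowed, and no timed observation after the stop is fixed.

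**Serious events are collected anyway.** This also stands, and it limits the point most. A reader might infer that rebound after EOI goes unrecorded, or that all detection then rests on someone suspecting it. Sections 8.2.2 and 8.3 do not support either reading. Serious falls are collected to day 28 under their own names, and any suspected rebound counts as an SAE, so closing the AE window does not lose a recognised case.

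**The assessor is blinded.** Section 5.3 has the study doctor assess rebound in the blender wean, and 10.2 keeps that doctor blinded. It would therefore go too far to infer that rebound is generally assessed with knowledge of the arm. The concern applies only where receiving staff make the assessment. If blender INO is continued because of rebound, EOI has not been reached and readings go on.

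**Layout.** The schedule in 6.1.7 cannot be read reliably in the text available. It appears to show a reading at EOI and an adverse-event review at follow-up. The first is at the stop, and 8.3 is the section that sets the AE window.

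**Conclusion.** The point holds in a limited form and is minor. By the protocol's own definitions, no planned 5-minute SpO2, heart rate or blood pressure reading follows the last of four weaning steps or an unplanned stop, and the window for non-serious events closes at the same instant. Serious-event capture and the primary analysis are unaffected.

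What is lost is an objective between-arm reading of early deterioration, to set beside clinician-suspected rebound. The documents give no rate for rebound after a short, weaned exposure, so the number of events missed cannot be sized. Weaning and short exposure make rebound less likely but do not exclude it.

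The wording of 8.2.2 is a smaller matter. Its time limit can be read as applying to death only or to rebound as well. With SAE collection to day 28 in 8.3, the first reading is the more natural one, but the sentence should say so.

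The count assumes that weaning follows 5.3 from 20 ppm. Patients moved to another INO device reach EOI without a step to 0 ppm and fall outside it.

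**What to change.** Keep EOI and all endpoints as they are.

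1. In both arms, extend extraction of SpO2, heart rate and blood pressure (6.1.2, 7.1.2) and AE recording (8.3) to 15 minutes after the blender is set to 0 ppm. The anchor exists in both arms because the blender is set to 20 ppm whatever the allocation. Use the study monitor while it is attached and the hospital chart otherwise, without requiring the crew to stay.
2. Report by arm, descriptively, the change from the last reading before 0 ppm. Change from t0 would mix rebound with loss of INO benefit and the effects of intubation.
3. List separately the patients moved to another INO device (2.5.1).
4. Reword 8.2.2, for example: *Suspected rebound reactions, whether before or after end of intervention, are reported to the sponsor as serious adverse events; so is any death before end of intervention.*

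**Cost.** Up to three extra time points per patient, or 3 x 54 = 162 at the minimum sample size. The monitor already records continuously during the intervention, and the chart is already the second source for heart rate, blood pressure and the SpO2 series (9.2). The downside is that some readings after handover will be missing or not at 5-minute spacing, which is a further reason to keep the comparison descriptive.
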